#### Main analyses

For analyses below, we will analyze as randomized and attempt to collect outcome data on non-completers, following the intent-to-treat principle. For Aims 1 and 2, each outcome will be modeled separately, and we will examine sex as a biological variable by including sex as a covariate to control for its relationship with the outcomes and the interaction of sex and intervention group to examine if there are differential effects by intervention group. For Aim 1 (H1.1 and H1.2), the outcome will be the pre- to post- percent change in cortisol for each session. A linear mixed model will be fit with the independent fixed effects variables of intervention and session (1 to 4). Subject will be a random effect. We will use an F-test to test the intervention effect. For Aim 2 (H2.1, 2.2, 2.3), our primary goal is to test mediation effects. Mediation effects will be estimated in an ANCOVA setting, fitting the appropriate mediation models using MPlus [66] and then testing indirect effects using the percentile bootstrap approach to estimate the indirect effect [55]. The mediation model with two-path mediation effects specifies that the intervention will act through the mediator on the outcome and also have a direct effect on the outcome. Each outcome model will have 3 key predictors (intervention, two proximal mediators), and control for T1 outcome and covariates described above. For testing cortisol as a mediator, we will use (1) the estimated average percent change estimated from the mixed model, and (2) the % change from pre-session 1 to post session 4. In addition, we will look at child and parent cortisol levels both separately and together (multiple mediation model) in order to fully assess if/how they function together as mediators. Thus, for any single outcome, up to 6 models will be examined. For all mediation models in Aim 2, we will assess goodness-of-fit (GOF) using standard GOF measures (comparative fit index, root mean square error of approximation, and root mean square residual). For Aim 3, an exploratory aim, we will use graphical plots and non-linear repeated measures models to model the trend in percent changes in cortisol within and between intervention groups across the 4 sessions for all participants and across 8 sessions for high risk participants.

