### Sample size and power analysis

We will recruit a total sample size of 228 child/parent dyads and assume 25% attrition to retain 170 child/parent dyads (85 dyads/group) at Time 2. The primary goal of this study is to examine mechanisms via the mediation effects of the AME intervention. We will use the percentile bootstrap method to estimate the indirect/mediated effect [55]. The sample size needed for this study is primarily driven by the power needed for the mediation hypothesis in Aim 2. Simulations of the two-path mediation model in Mplus [56] show that 170 subjects are needed to have 88% power to test the total indirect effect using the Sobel approach when the effect of the independent variable (AME in this case) on the mediator is at least medium (13% of variation explained), mediator on the outcome is between small and medium (7% of variation explained), and independent variable on the outcome is small (2% of variation explained). Via simulation, the Type I error with this sample size under a model that assumes no indirect effect is also less than 0.007, which will readily accommodate the multiple comparison adjustments planned below (e.g. with 7 cytokines a conservative Bonferroni adjustment would be 0.05/7 = 0.007). A sample size of 170 will also afford 90% power to detect a medium effect size for H1.1 and H1.2 based on a two-sample t-test with a two-sided alpha level of 0.05. Fitting models that allow for repeated measures across session will result in improved power. Using the percentile bootstrap method instead of Sobel should afford the same or greater power.

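### The sex-by-intervention interaction is not kept apart from the Aim 1 F-test, so the effect tested may not be the two-group contrast behind the stated 90% power

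*Protocol article*

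**What the plan says.** The Main analyses section says that each Aim 1 and Aim 2 outcome is modelled separately. Sex is examined by "including sex as a covariate to control for its relationship with the outcomes" and, in the same clause, by including "the interaction of sex and intervention group to examine if there are differential effects by intervention group". For Aim 1 it then names a linear mixed model for the percent change in cortisol, with intervention and session as fixed effects and subject as a random effect, and adds: "We will use an F-test to test the intervention effect". For Aim 2 it lists the intervention, two mediators, the baseline outcome and the covariates, and tests indirect effects with a percentile bootstrap.

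The Preliminary analyses section puts both child sex and parent sex in all models. No section says whose sex enters the interaction.

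The Sample size and power analysis section states: "A sample size of 170 will also afford 90% power to detect a medium effect size for H1.1 and H1.2". The calculation behind this figure is a plain t-test of two groups, two-sided at 0.05. The 170 come from "assume 25% attrition to retain 170 child/parent dyads (85 dyads/group) at Time 2". It adds: "Fitting models that allow for repeated measures across session will result in improved power".

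**The concern.** H1.1 and H1.2 each state one overall comparison of AME with control, and the power statement treats them that way. Once a sex-by-intervention term is in the model, there is no longer a single intervention effect that every analyst would test. Under indicator coding, the intervention coefficient is the effect in the reference sex. Under a Type III test, it is the mean of the two sex-specific effects with half the weight on each, however few people one sex contributes.

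If the true effect is the same in both sexes, the equal-weight target has the same value and only precision suffers. If the effects differ, the target changes too. In either case a confirmatory result could depend on a software default that the article does not fix. The parent analysis (H1.2) is the more exposed, because one parent of either sex attends and the split could be uneven.

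**Working it through.** **Inputs.** From the sample size section: 85 per group, two-sided alpha 0.05, two-sample t-test, medium effect. Assumed, because the article does not give them: d = 0.5 for medium; the share p of the more common sex, equal in both arms; the within-subject correlation rho across sessions; and the same true effect in both sexes.

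**Step 1: the stated figure.** The noncentrality is 0.5 × √(85/2) = 0.5 × √42.5 = 3.26. With 168 degrees of freedom, power is 90.0%. The stated 90% reproduces for a model without the interaction.

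**Step 2: interaction retained, one measurement.** With equal weight on each sex, the variance is multiplied by 1/[4p(1−p)], so the noncentrality is 0.5 × √(42.5 × 4p(1−p)). With indicator coding, only the reference sex (share q) informs the test, so it is 0.5 × √(42.5 × q). There are 166 degrees of freedom. At 85:15:
- Type III: 4 × 0.85 × 0.15 = 0.51, noncentrality 2.33, power 64%.
- Minority sex as reference: 0.5 × √(42.5 × 0.15) = 1.26, power 24%.
- Majority sex as reference: 0.5 × √(42.5 × 0.85) = 3.00, power 85%.

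| Sex split | 4p(1−p) | Type III | Reference = minority | Reference = majority |
|---|---|---|---|---|
| 50:50 | 1.00 | 90% | 63% | 63% |
| 70:30 | 0.84 | 84% | 43% | 77% |
| 80:20 | 0.64 | 74% | 31% | 83% |
| 85:15 | 0.51 | 64% | 24% | 85% |
| 90:10 | 0.36 | 49% | 18% | 87% |

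**Step 3: allow for repeated measures.** The mean of four sessions has variance (1 + 3rho)/4 times that of one session: 0.40, 0.625 and 0.775 for rho of 0.2, 0.5 and 0.7. Dividing the Type III term by this factor gives:

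| Sex split | rho 0.2 | rho 0.5 | rho 0.7 |
|---|---|---|---|
| 50:50 | 99.9% | 98% | 96% |
| 80:20 | 98% | 91% | 84% |
| 85:15 | 96% | 83% | 75% |
| 90:10 | 87% | 69% | 60% |

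The 50:50 row is also, in effect, the power without the interaction. Power stays at 90% or more while 4p(1−p) is at least (1 + 3rho)/4, that is, up to a split of about 89:11, 81:19 or 74:26 for the three correlations.

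**Step 4: does the fix work?** A simulation (4,000 runs per split, one measurement) with sex as a main effect only gave 89.5%, 90.4%, 90.3% and 90.4% at 50:50, 80:20, 85:15 and 90:10. The Type III test in the same runs gave 89.3%, 72.8%, 61.9% and 47.1%, close to the table.

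**Step 5: Aim 2.** The indirect effect is the product of the intervention-to-mediator path and the mediator-to-outcome path. An interaction placed only in the outcome equation makes the direct effect sex-specific and leaves both of those paths alone, so one indirect effect remains. If the term also enters the mediator equation, the first path differs by sex, and so does the indirect effect.

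**The case against.** The strongest reply is that the article never says the interaction sits in the tested model. The Aim 1 fixed effects are listed as intervention and session, the Aim 2 predictors are listed without the interaction, and the interaction has its own stated purpose of looking for differential effects. A separate model, or a Type II test, would fit the text and keep the ordinary average. Model sequence is also often left to an analysis plan.

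Part of this stands: the text is ambiguous, and an error is not proven. But the Aim 1 list also leaves out the covariates that Preliminary analyses puts in all models, so its silence does not exclude the interaction. The literal wording puts sex and the interaction into the outcome models together, and no later sentence separates them. The Aim 2 count of up to 6 models per outcome is already used up by two mediator definitions times child, parent or both (2 × 3 = 6), which leaves no visible place for separate interaction models.

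The reply is also right on size. A reader might infer from the single-measurement figures that the 90% is lost for parents. The documents do not support that, because the sex split and rho are unknown and the planned repeated measures may offset some or all of the loss. Nor should the 24% be quoted alone: with the majority sex as reference the figure is 85%.

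**Conclusion.** The point holds as an ambiguity with a conditional cost. Read literally, the plan lets the H1.1 and H1.2 F-tests target something other than the contrast that was powered.

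- **Parents (H1.2):** power may fall below 90%. Under Type III with four sessions, this needs a split more uneven than about 89:11, 81:19 or 74:26 at rho 0.2, 0.5 or 0.7. Whether the trial will be there cannot be told from the article.
- **Children (H1.1):** if the split is near 50:50 (assumed), a Type III test costs nothing. Testing an indicator-coded coefficient would give 63% on one measurement.
- **Aim 2:** a reader might infer that no single indirect effect is left to bootstrap. That follows only if the interaction also enters the mediator equation, which the article does not say. The F-test and the 90% figure belong to Aim 1; Aim 2 has its own 88% power figure.

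All sizes rest on d = 0.5, equal effects in both sexes, the same sex split in both arms and, for the repeated-measures figures, a simple mean of four equally correlated sessions.

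**What to change.** State in Main analyses that the F-tests for H1.1 and H1.2 and the primary Aim 2 indirect effects come from models with sex as a main effect only. State that the sex-by-intervention interaction is tested in a separate secondary model, with sex-specific estimates, and name for each outcome whether child or parent sex is used.

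The cost is a short change of wording and one extra secondary model per outcome. Sample size and data collection do not change, and the planned look at sex as a biological variable is kept.

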**Methods:**

This two-group randomized controlled trial (R01NR019190) is designed to examine biological mechanisms of effect and dose-response relationships of AME on child/parent stress during the consolidation phase of Acute B- or T-cell Lymphoblastic Leukemia (ALL) and T-cell Lymphoblastic Lymphoma (TLyLy) treatment. Child/parent dyads (n = 228) are stratified (by age, site, risk level) and randomized in blocks of four to the AME or attention control condition. Each group receives one session (30-minutes AME; 20-minutes control) during weekly clinic visits (4 weeks standard risk B-cell ALL; 8 weeks high risk B-cell ALL/T-cell ALL/TLyLy). Parents complete questionnaires at baseline and post-intervention. Child/parent salivary cortisol samples are taken pre- and post-session (sessions 1–4). Child blood samples are reserved from routine draws before sessions 1 and 4 (all participants) and session 8 (high risk participants). We will use linear mixed models to estimate AME’s effect on child/parent cortisol. Examining child/parent cortisol as mediators of AME effects on child and parent outcomes will be performed in an ANCOVA setting, fitting the appropriate mediation models using MPlus and then testing indirect effects using the percentile bootstrap approach. Graphical plots and non-linear repeated measures models will be used to examine dose-response relationship of AME on child/parent cortisol.

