###  Hypothesis 2.1

Reductions in child and/or parent cortisol will mediate the effect of AME on child immune function.

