**Child Outcomes**					
Child Immune Function	Immunomodulatory Cytokines (Blood)*	N/A	N/A	Pre-Sessions 1, 4, 8	Nurse/ Phleboto-mist
Child Emotional Distress	CHQ – *Mental Health Subscale*[61]	16	0.81†	T1, T2	Parent
Child Quality of Life	KINDL^R^ [62]	20	0.89†	T1, T2	Parent

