#### Biologic sample collections and storage during clinic visits

This study collects both saliva and blood. Both child and parent (caregiver) provide saliva for the detection of cortisol levels. Saliva collections occur before and after each intervention or attention control session at all 4 sessions for standard risk participants and the first 4 sessions for high-risk participants. The saliva is collected in a Salimetrics SalivaBio Oral Swab or SalivaBio Children’s Swab for the caregiver and child, respectively. The swab is immediately placed in the prelabeled storage tube, placed on dry ice post-collection, and stored at -80 C.

Blood is only collected from the children. At each site, 5 mL of blood is collected as part of routine study draws the morning of their sessions and used to isolate serum for cytokine analysis. This occurs at sessions 1 and 4 for all children with an additional draw at session 8 for high-risk children. Our primary site collects an additional 1 mL of blood to conduct a blood cortisol analysis for the purpose of monitoring adrenal function in a subset of the children on study. These collections occur at the child’s end of induction clinic appointment as well as sessions 1 through 4. Serum for cytokine analyses will be held until the end of the study at which point multiplexed analyses will be run. Serum for monitoring adrenal function in the children will be run on a yearly basis.

Treating physicians, at our three hospitals, have assigned clinic days and times (morning vs. afternoon). This will minimize variability in the timing of saliva collection between appointments. We will track day/time of collections and other factors that may contribute to child and parent cortisol interpretation (i.e., sleep, food/drink intake, medications).

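### H2.1: for cytokines drawn before session 4, mediator (2) ends after the outcome and mediator (1) includes one of four session changes that falls after it

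*Protocol article*

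**What the plan says.** All references are to the protocol article.

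- **Hypothesis.** Hypothesis 2.1: "Reductions in child and/or parent cortisol will mediate the effect of AME on child immune function".
- **Outcome timing.** Abstract, Methods: "Child blood samples are reserved from routine draws before sessions 1 and 4 (all participants) and session 8 (high risk participants". Table 2 lists the cytokines at "Pre-Sessions 1, 4, 8". The section on biologic sample collections says "5 mL of blood is collected as part of routine study draws the morning of their sessions" and then "This occurs at sessions 1 and 4 for all children with an additional draw at session 8 for high-risk children".
- **Mediator timing.** Saliva is collected before and after each session "at all 4 sessions for standard risk participants and the first 4 sessions for high-risk participants".
- **Mediator definitions.** Main analyses gives two: "1) the estimated average percent change estimated from the mixed model", from a model whose session factor runs from 1 to 4, and "2) the % change from pre-session 1 to post session 4". They serve H2.1, H2.2 and H2.3 alike, with no exception for cytokines. Child and parent cortisol are each entered alone and together, giving up to six models per outcome.

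The article does not say whether the session-4 or the session-8 draw is the H2.1 outcome.

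**The concern.** A mediation model reads the association between mediator and outcome as the effect of the first on the second, so the mediator has to come first. Standard-risk children have four sessions, so the blood taken before session 4 is their only follow-up cytokine value. Neither session 4 nor the cortisol change across it can have influenced that blood. Any association between the session-4 change and those cytokines must come from the cytokines (or the immune state behind them) acting on later cortisol, or from a shared cause.

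The sample size section calls mediation the primary goal and lets it drive the sample size. An indirect effect for H2.1 that could reflect the reverse direction would weaken the biological claim the trial is built to test.

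**Working it through.** **1. Order of samples around the session-4 draw**

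| Quantity | Sessions used | Position relative to the draw before session 4 |
|---|---|---|
| Mediator (1) | changes in sessions 1, 2, 3, 4 | three before, one (1/4 = 25%) after |
| Mediator (2) | pre-session 1 and post-session 4 | starts before, ends after |

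The article does not give the order of the blood draw and the pre-session-4 saliva. Only the post-session-4 saliva is certainly later, but the session-4 change and the end point of mediator (2) both depend on it.

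For the session-8 draw (high-risk children only), all the saliva was collected about four weeks earlier, so the order is correct. T2 questionnaires follow the last session, so H2.2 and H2.3 are also in order.

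**2. Extent.** Seven cytokines with up to six models each give up to 7 × 6 = 42 session-4 models. Half of them, 21, use mediator (2).

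**3. The plan's own power figure.** Inputs from the sample size section: n = 170 (85 per group), and 13%, 7% and 2% of variation for AME to mediator, mediator to outcome and AME to outcome. The standardised paths are √0.13 = 0.361, √0.07 = 0.265 and √0.02 = 0.141. A two-sided alpha of 0.05 is assumed for the Sobel test, because the article states it only for the t-test. Over 10,000 simulated trials, power is 88.4%, against 88% stated. The figure reproduces.

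**4. Cost of ending mediator (1) at session 3.** The reliability of a k-session mean is k·ICC / [1 + (k − 1)·ICC]. The ICC between sessions is not in the article. At an assumed 0.3:

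- four sessions: 1.2/1.9 = 0.63
- three sessions: 0.9/1.6 = 0.56
- ratio: 0.5625/0.6316 = 0.89

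Scaling the 13% and 7% by this ratio gives 11.6% and 6.2%. Repeating the simulation (4,000 trials per row):

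| Assumed ICC | Ratio | Sobel power at 0.05 |
|---|---|---|
| 0.1 | 0.81 | 78% |
| 0.2 | 0.86 | 80% |
| 0.3 | 0.89 | 83% |
| 0.5 | 0.94 | 86% |
| 0.7 | 0.97 | 87% |

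These powers take no account of multiplicity. At 0.05/7 = 0.007, the strictest step for seven cytokines, the same simulations give 54% for four sessions and 41% for three at ICC 0.3. The calculation treats sessions as exchangeable and applies to mediator (1) only. Mediator (2) has one start and one end sample under either definition.

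**5. Using only session-8 cytokines instead.** The high-risk share is not in the article. If 30%, 40%, 50% or 60% of the 170 are high risk (51, 68, 85 or 102 children), Sobel power at 0.05 is about 17%, 29%, 44% or 58%.

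**6. Possible false positives (illustration only).** Assume n = 170, ICC 0.3, no effect of cortisol on the cytokine, and a cytokine that shifts the session-4 cortisol change by g SD per SD. There is no baseline adjustment. The table gives the share of Sobel tests significant at 0.05 over 3,000 trials:

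| g | Mean of sessions 1–4 | Mean of sessions 1–3 | Session 4 alone |
|---|---|---|---|
| 0 | 3% | 3% | 2% |
| 0.2 | 11% | 3% | 54% |
| 0.3 | 24% | 3% | 88% |
| 0.5 | 58% | 4% | 97% |

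The last column is only a rough stand-in for mediator (2), which is also defined relative to pre-session 1. The article gives no value for g.

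**The case against.** The case against a broader reading is strong, and most of it stands.

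- A reader might infer that both mediators are measured after the outcome. The documents do not support that: three of the four session changes in mediator (1) are complete before the draw.
- A reader might infer that a significant indirect effect would give H2.1 no support. That goes too far. A result carried by sessions 1 to 3, or one found with the session-8 draw, is correctly ordered. The fair word for the session-4 result is ambiguous.
- Adjusting for the T1 outcome removes part of any stable link between cytokines and cortisol. It does not restore the order.
- Two of the six models per outcome use parent cortisol alone. A reverse path there would need the child's cytokines to move the parent's cortisol, which is less plausible. It remains true that session 4 cannot have acted on blood already drawn.
- The false-positive rates depend on an assumed g. At g = 0 there is no inflation, so they show what could happen and do not estimate the bias.
- Dropping session 4 is not free. The discussion of the second biomarker challenge expects the AME advantage to grow over time, so session 4 may carry the largest contrast. The reliability formula cannot show that loss.

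It can also be said that the choice of draw may be left to the SAP. That is fair as to the draw. The mediators and the blood schedule, however, are both fixed in the article, and for standard-risk children they conflict whichever draw high-risk children contribute.

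**Conclusion.** The concern holds for H2.1 with the session-4 cytokines. Mediator (2) ends after the outcome, and mediator (1) does so for one of its four session changes. This affects every standard-risk child and any all-participant analysis at session 4. A significant indirect effect there could not be read cleanly as cortisol acting on cytokines, and mediator (2) is the weaker of the two.

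The timing conclusion needs no assumption beyond the published schedule. The size of any bias cannot be determined from the article. The stated 88% power is arithmetically sound; it simply presumes a mediator that precedes the outcome. Aim 1, H2.2, H2.3 and the session-8 cytokines stand as written.

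**What to change.** 1. Name the H2.1 outcome: session-4 cytokines for all children, with session-8 cytokines as a secondary outcome in high-risk children only.
2. For session-4 cytokines, use only cortisol collected before that draw: (1) the average percent change from the mixed model refitted to sessions 1 to 3, so that session 4 does not enter the subject estimates, and (2) the percent change from pre-session 1 to post-session 3.
3. Keep the session 1 to 4 mediators for session-8 cytokines and the T2 outcomes.
4. Report the session 1 to 4 mediators with session-4 cytokines only as a sensitivity analysis, stating that part of the mediator follows the outcome.

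This changes analysis wording only. It needs no new samples and keeps all 170 dyads. The serum is to be held for assay until the end of the study, so the change can be made before any cytokine result exists. The price is one session fewer in the mediator, with the power loss shown in step 4 of the working, and possibly more if the AME effect builds over sessions.

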###  Hypothesis 2.2

Reductions in child and/or parent cortisol will mediate the effect of AME on *child* emotional distress and quality of life.

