#### Missing data and multiple comparisons

We will compare all baseline variables between subjects who drop out of the study and those who do not using two-sample *t* tests, chi-square tests, or non-parametric equivalents as appropriate. MPlus software will incorporate participants who drop out before completion by using the MPLUS imputation method to perform a bias adjustment for missing data under maximum likelihood estimation and the assumption that data are missing at random. If we find that missing data are not missing at random, we will use a pattern mixture modeling approach to address; note we expect up to 25% attrition but minimal missing data on instruments (< 1%). We will adjust *p* value for multiple comparisons using the Bonferroni method for parent emotional/traumatic distress as there are two outcomes for this domain. For cytokine analyses, there are 7 cytokines of interest, so a Hochberg step-up approach will be used for these analyses.

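### Aim 2 tests each outcome in up to six mediation models with none labelled primary, and the stated multiplicity rules adjust only across outcomes

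*Protocol article*

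**What the plan says.** Under Main analyses, the article says that testing mediation is the primary goal of Aim 2. The Sample size and power analysis section makes it the primary goal of the whole study and sizes the trial on it.

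- **Mediator definitions.** There are two: "1) the estimated average percent change estimated from the mixed model, and (2) the % change from pre-session 1 to post session 4".
- **Mediator sets.** There are three: "we will look at child and parent cortisol levels both separately and together (multiple mediation model"). Two times three gives the six: "Thus, for any single outcome, up to 6 models will be examined".
- **Possible lead model.** The same section says "Each outcome model will have 3 key predictors (intervention, two proximal mediators"). This describes the joint model but does not call it primary.
- **Test.** The plan is "testing indirect effects using the percentile bootstrap approach".
- **Hypotheses.** H2.1–H2.3 share the opening "Reductions in child and/or parent cortisol will mediate the effect of AME on".
- **Multiplicity.** Missing data and multiple comparisons adjusts "using the Bonferroni method for parent emotional/traumatic distress as there are two outcomes for this domain", and applies Hochberg to the seven cytokines. Child distress, child quality of life and parent quality of life get no adjustment. Nothing is said about the six models within an outcome.
- **Type I error.** Sample size and power analysis gives a simulated type I error below 0.007 under no indirect effect. It says this leaves room for the planned adjustments, with the seven cytokines as the example.

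**The concern.** The article sets out its multiplicity plan, and that plan does not cover the multiplicity the article itself creates. With the and/or wording, six models and no lead model, there are several routes to declaring mediation for one outcome. If the models disagree, no rule says which one decides.

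At stake is the error rate for the study's primary goal. Bonferroni over two scales or Hochberg over seven cytokines controls error across outcomes only if each outcome contributes one valid p-value. The best of six is not one.

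The null that matters is that AME lowers cortisol but cortisol does not drive the outcome. Aim 1 expects the first half of that, so the case is realistic.

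A second issue concerns "1) the estimated average percent change estimated from the mixed model". The Aim 1 mixed model has intervention as a fixed effect and subject as a random effect. If each subject's prediction from it is exported and treated as data, the prediction keeps the full arm difference but has less spread within arms.

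**Working it through.** **Inputs from the article.** n = 170 (85 per arm). AME explains 13% of mediator variance, the mediator 7% of outcome variance, and the direct effect 2%. Two-sided 0.05 is stated for H1.1 and H1.2 and assumed here for each Aim 2 test. Models per outcome: 2 × 3 = 6.

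**Assumed, because the article gives no values.** Child–parent correlation, correlation between the two cortisol definitions, and between-session correlation. Ranges are shown.

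**1. The plan's own figures.** Take a = √0.13 = 0.361, b = √0.07 = 0.265, c′ = √0.02 = 0.141, with one mediator, the Sobel test and 10,000 simulated trials. Power is 87.9%, against the stated 88%. Sobel type I error in the same set-up:

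- both paths null: 0.0004
- AME affects cortisol, cortisol does not affect the outcome: 0.032
- AME does not affect cortisol, cortisol affects the outcome: 0.017

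Only the first is below 0.007. With the planned percentile bootstrap, in the second case at correlations 0.3 and 0.5, single tests ran at 0.044–0.061.

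**2. Simple bounds.** Six tests at the article's 0.007: 6 × 0.007 = 4.2%. Six independent tests at 0.05: 1 − 0.95⁶ = 26.5%.

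**3. Six models simulated.** Four single-mediator models plus the total indirect effect in two joint models. Percentile-bootstrap 95% intervals, b = 0, 1,500 trials per row. Monte Carlo standard error near 20% is √(0.2 × 0.8 / 1500) ≈ 1 point.

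| AME effect on cortisol | Child–parent corr. | Definition corr. | At least one of six significant |
|---|---|---|---|
| 13%, all mediators | 0 | 0 | 24.6% |
| 13%, all | 0.3 | 0.3 | 21.2% |
| 13%, all | 0.3 | 0.5 | 20.0% (21.5% in a second run) |
| 13%, all | 0.3 | 0.7 | 18.8% |
| 13%, all | 0.5 | 0.7 | 16.8% |
| 13%, all | 0.6 | 0.9 | 13.9% |
| 6%, all | 0.3 | 0.5 | 16.5% |
| 2%, all | 0.3 | 0.5 | 10.1% |
| 13%, child only | 0.3 | 0.5 | 12.6% |
| 13%, one definition only | 0.3 | 0.5 | 9.7% |
| none | 0.3 | 0.5 | 0.9% |

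Other simulations of the 13% case over child–parent 0.2–0.5 and definition 0.4–0.7 gave values down to 15%. The 2% case also came out at 8%.

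**4. By test level (13%, all mediators, 0.3 and 0.5).** At 0.025: 12.9% (11–13% across runs). At 0.05/7: 4.7%. At 0.05/6: 5.1%. The two joint models alone at 0.05: 9.9% (7–10% across runs).

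**5. Session-averaged mediator, if exported as a prediction.** With four sessions and between-session correlation ρ, the within-arm deviation is multiplied by λ = 4ρ/(1 + 3ρ) while the arm difference is kept. The standard error of the AME-to-cortisol path is therefore too small by the factor λ, and its nominal 5% test rejects at about 2[1 − Φ(1.96λ)]. The simulations are of the indirect effect, with no AME effect on cortisol and fixed predictions.

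| ρ | λ | Formula, AME-to-cortisol path | Simulated indirect-effect test |
|---|---|---|---|
| 0.2 | 0.8/1.6 = 0.50 | 33% | 29–32% |
| 0.3 | 1.2/1.9 = 0.63 | 22% | 20–23% |
| 0.5 | 2.0/2.5 = 0.80 | 12% | 10–14% |
| 0.7 | 2.8/3.1 = 0.90 | 8% | 7–8% |

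The raw session mean gave 4–6%. Recomputing the prediction inside every bootstrap resample gave 5%, 4% and 7% at ρ = 0.2, 0.3 and 0.5.

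**The case against.** **A flat 20% error rate.** A reader might infer that every Aim 2 outcome carries a false-positive rate of about 20% instead of 5%. The documents do not support that. Of 12 outcomes (7 cytokines, 2 parent distress scales, 3 others), only the last three are tested at an unadjusted 0.05. Even there, the figure needs AME to move all four mediators as planned and cortisol to do nothing. This stands and limits the size of the point.

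**The stated type I error.** At face value, below 0.007 per test caps six models at 4.2%. But that figure is reproduced only with both paths null, and it accompanies a Sobel calculation. It does not cover the planned bootstrap when AME lowers cortisol as expected.

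**An implied lead model.** The article describes outcome models with two mediators and powers the total indirect effect; the separate and joint looks are introduced as an addition. A joint lead model is a fair reading. It is not labelled as such, and two cortisol definitions remain, giving 7–10%. This narrows the point without removing it.

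**Left to the analysis plan.** An unshown plan may rank the models. Still, the article states its multiplicity rules and the six models together, and the first do not cover the second.

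**The exported prediction.** A reader might infer that the session-averaged mediator makes the mediation test invalid. The article does not say that predictions are exported and held fixed. If they are recomputed in each resample, error stays near nominal, and at high between-session correlation the inflation is small. This strand is conditional.

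**Conclusion.** The point holds as a gap in error control for the study's primary goal: up to six models per outcome, none labelled primary, and no adjustment across them.

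The size depends on what is true:

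- **Three unadjusted outcomes.** About 15–21% if AME explains 13% of every cortisol mediator and cortisol does not affect the outcome, for the moderate correlations assumed; 14–25% over wider ones. About 8–10% if AME explains 2%, 10–13% if it moves only the child's cortisol or only one definition, and about 1% if both paths are null.
- **Parent distress scales at 0.025.** About 11–13% in the planned-effect case.
- **Cytokines.** About 5% at Hochberg's strictest step, 0.05/7; later steps are less strict.

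The exported-prediction issue is secondary. It applies only if fixed subject predictions are treated as observed data, and its size rests on between-session correlations that the article does not give.

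**What to change.** Name one cortisol definition and one primary model per outcome. The joint child–parent model, tested on its total indirect effect, is the natural candidate because the power calculation and the description of the outcome models both point to it. Report the specific child and parent indirect effects alongside. State that the other models are sensitivity analyses that cannot alone support H2.1–H2.3.

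The alternative is to adjust across the six. At 0.05/6 per model the simulated rate is about 5% in the planned-effect case, at some loss of power.

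For the session-averaged mediator, say how it is computed. Options are a latent session mean inside Mplus, which keeps dyads with missed sessions; the observed session mean, which gives up the mixed model's handling of missed sessions; or refitting the mixed model within each bootstrap resample.

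The cost is wording only, with no new data or dyads. The other models lose confirmatory status. A total indirect effect alone does not say whether child or parent cortisol mediates and can hide opposing paths, which is why the specific effects should be shown.
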